#### 6-month follow-up

The same procedure will be used for the six-month follow-up. If it is not possible to contact the participant after six attempts, he/she will be recorded as lost to follow-up.

### Questionnaire survey and interviews with intervention deliverers

In order to assess the acceptability of the iQuit intervention for those delivering the intervention and to assess the feasibility of the intervention and aspects of the trial design, SCAs will be invited to complete a postal questionnaire, providing feedback on the programme including research elements such as practice support, audio recording and managing paperwork. A sub-sample of SCAs, consisting of nurses and HCAs from high and low recruiting practices will be purposively sampled to participate in semi-structured interviews to canvass their views on participating in the study.

Interviews will be completed at the practice, last up to one hour and be audio recorded and transcribed verbatim.

### Outcome measures

#### Effectiveness

(i) Primary outcome measure

The primary outcome measure of effectiveness will be self-report of being abstinent from smoking for at least two weeks at eight-week follow-up from randomisation date, as assessed by postal questionnaire or telephone interview.

(ii) Secondary outcome measures

Secondary outcome measures will include:

(a) CO-verified self-report of being abstinent from smoking at four-week follow-up from quit date for at least two weeks, assessed at an appointment with the SCA. (We will use the definition recommended for use by local Stop Smoking Services in England [31]: a CO reading that is assessed 25 to 42 days from quit date and is less than 10 parts per million.)

(b) Self-reported prolonged abstinence (at least 3 months) at six-month follow-up from randomisation date, assessed by postal questionnaire or telephone interview. Because follow up will be conducted by post and/or telephone call with a research interviewer, we do not plan to validate self-reports at six months [32]. Furthermore, it would be difficult to bring participants into the surgery for an additional CO measure at this time point. The main alternative, obtaining saliva samples by post for cotinine assay, has several disadvantages: it may yield a low response rate; measuring cotinine at one time point cannot validate prolonged abstinence; smoking behaviour may change between the questionnaire and receipt of the saliva kit; it is impossible to check whether a returned saliva sample is from a particular participant – samples may be substituted; and a significant proportion of participants may still be using nicotine replacement at follow up.

#### Feasibility

Measures for assessing feasibility will include: the proportion of practices approached who agree to participate; the proportion of smokers who respond to the proactive recruitment letter; the number of smokers per practice recruited into the study in a six-month period; response rates to postal follow-up questionnaires; increase in length of consultation.

#### Acceptability

(i) To the SCAs

SCAs’ evaluation of using the iQuit program, as assessed by postal questionnaire (how easy was it to use; how helpful they found it; how it could be improved; would they continue to use it if it were available).

(ii) To the participants (intervention group only)

(a) Participants’ evaluation of the printed advice report, as assessed by postal questionnaire at eight weeks (whether they kept the report; how much of it they read; how clear, useful and relevant the advice was; what they particularly liked and disliked about the report).

(a) Participants’ evaluation of the text messaging component, as assessed by postal questionnaires at eight weeks and six months (e.g. how useful and relevant they found the messages; whether there were too many or not enough; whether they covered the right topics; how the system could be improved).

(a) Proportions of participants who used the HELP and SLIP features; frequency of use.

(a) Proportion of participants who texted STOP to stop receiving further messages; when they did this (number of days into the program); why they did this (assessed on 6-month follow-up questionnaire).

### Sample size, power and precision

This is a proof-of-concept trial designed to yield information about the acceptability, feasibility and short-term effectiveness of the intervention, but not to give a definitive answer to the question of whether the intervention is effective in the longer term.

For effectiveness, we have chosen to power the study on outcome at eight weeks (self-reported abstinence for at least 2 weeks at 8 week follow-up from randomisation date). A sample size of 300 per group would give 80% power to detect an increase in quit rate from 20% to 30% (alpha = 0.05, 2-sided test).

The six-month outcome will provide valuable additional information. For comparison between groups at six-month follow-up, a 95% confidence interval will be calculated to estimate the precision of the estimate of the difference in quit rates. Assuming a six-month quit rate of 8% in the control group, based on pooled rates observed in similar control groups reported in a Cochrane review of self-help [7], an observed increase of 5% in the six-month quit rate from 8% to 13% (RR 1.65) would be estimated with an accompanying 95% confidence interval having a width of +/-5%, given the trial size of 600. Such an observed increase would be borderline statistically significant, though the trial is limited to having 51% power to detect a true underlying difference of 5% as statistically significant and a larger trial would be needed to distinguish reliably a true increase from a Type 1 error. Importantly, if a 5% increase is observed, then an underlying population relative risk of 1.5 or higher will be estimated to exist with posterior probability 74%, using a Bayesian statistical approach where no prior information is added to that obtained through the trial. This probability will inform the decision of whether to proceed to a larger, pragmatic trial; the 95% confidence interval would then be used to inform the choice of a plausible and worthwhile effect size from which to power this trial with a primary outcome of six-month or 12-month quit rate.

### Statistical analysis

An analysis plan will be prepared by the study statistician prior to analysis. The two groups will be compared using chi-squared tests and logistic regression analysis for binary outcome measures, and independent t-tests, analysis of variance and linear regression analysis for continuous measures. All tests will be two-sided using an alpha of 0.05.

The main analyses of quit rates will be conducted on an intention-to-treat basis, making the usual assumption that participants lost to follow up are smoking, although we will also conduct sensitivity analyses using a range of less severe assumptions informed by available baseline and interim data [33]. A further sensitivity analysis will involve estimating the intervention effect allowing for clustering of participant outcomes by household. As the mean cluster size (participants per household) will be close to 1, the results and conclusions are not expected to be materially different from the main analysis. The intra-household correlation coefficient will be estimated in order to inform the design and sample size of any subsequent trial.

Proportions, such as many of the secondary outcomes of acceptability and feasibility, and loss to follow up, will be reported overall and for each arm and compared between arms with a p-value from Fisher’s exact test and a 95% confidence interval calculated by the Clopper-Pearson method. Proportions that are defined in a single arm will be estimated with an exact 95% confidence interval using the binomial distribution.

Additional analyses will include an examination of potential effect modifiers (i.e. was the intervention more effective in particular subgroups of smokers?), predictors of quit attempts and success in quitting, and a comparison of study quit rates with NHS reported rates. The cost of delivering the intervention will be assessed in terms of the average length of the consultation in the two conditions.

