### Procedure: initial consultation

Once the patient has consented to participate in the study, the SCA will provide brief smoking cessation advice, as per usual practice. The participant is required to set a quit date within the next 14 days. Expired-air CO level will also be measured. The CO monitors will be calibrated regularly by the study team.

During the consultation, the SCA will log on to the web-based iQuit program via the practice computer using a personal SCA identification number. The SCA will be prompted to enter answers to the first set of questions (Part 1) on the online questionnaire, as they complete it in consultation with the participant. These questions, which will be completed for all participants in the study, include gender, age, cigarette consumption, longest period of abstinence, strength of motivation and determination to quit smoking, and quit date (which must be in the next 14 days). The SCA will also enter the participant’s CO level on the questionnaire. This information will be used to characterise the sample and to check the baseline comparability of the intervention and control groups.

For those participants randomised to the Control group, only the first set of questions on the online questionnaire will be completed and no advice report will be generated. For those participants randomised to the Intervention group, the SCA will ask a second set of questions (Part 2) and will enter the answers on the online questionnaire. The 17 questions in Part 2 include whether participants think of themselves as addicted to smoking, most important reason for quitting, most difficult situation in which to resist smoking, main advantage and main disadvantage of quitting, whether they live with other adults who smoke, whether they have any health problems linked with smoking, and their mobile phone number. The answers to both sets of questions (Part 1 and Part 2) will be used to generate the tailored advice report. The SCA prints out the report and gives it to the smoker and then concludes their routine support by arranging a prescription for NRT or other pharmacological treatment, if appropriate, and arranging a routine NHS follow-up visit four weeks from the quit date. Some practices may also conduct interim follow-up visits according to their standard practice.

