During the baseline and four-week follow-up consultations, the SCA will manually complete case report forms (CRFs). These will record data collected by the NHS routinely for smoking cessation targets (including ethnic group, occupation code, smoking cessation medications prescribed, outcome) to allow comparison of study quit rates with NHS reported rates. The SCA will manually record the time at start and completion of the CRFs, and the iQuit program will record the time taken to complete the first and second set of questions on the online questionnaire.

Participants randomised to the Intervention group will be sent tailored text messages from a web server at the study centre over a three-month period, starting the day before their quit date. To cover any costs associated with receiving and sending text messages for the study, intervention participants will be sent a £5 voucher, posted out with the eight-week follow-up questionnaire. Control participants will not be sent any text messages.

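### Controls also complete Part 1 of the iQuit questionnaire, so the between-arm difference in consultation length is only a lower bound for the time iQuit adds to usual care

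*Protocol article*

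**What the plan says.** Statistical analysis in the Protocol article states: "The cost of delivering the intervention will be assessed in terms of the average length of the consultation in the two conditions". The Feasibility list of outcome measures ends with "response rates to postal follow-up questionnaires; increase in length of consultation".

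Procedure: initial consultation sets out what each arm does. On Part 1 it says: "These questions, which will be completed for all participants in the study, include gender, age, cigarette consumption". For controls, "only the first set of questions on the online questionnaire will be completed and no advice report will be generated". Intervention participants go on to Part 2, which has 17 questions. On the use of the answers it says: "The answers to both sets of questions (Part 1 and Part 2) will be used to generate the tailored advice report". The Randomisation section places allocation immediately after Part 1 is submitted.

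The same procedure section plans the timing data: the "iQuit program will record the time taken to complete the first and second set of questions on the online questionnaire". The section on audiotaping adds that a sample of recorded consultations in both arms will supply timing information. Usual care, described under Control, contains no online questionnaire, but it does include talk about smoking habits and history, a CO reading and advice on setting a quit date.

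**The concern.** The useful quantity for a practice or a later trial is the adviser time that iQuit adds to ordinary care. The control consultation in this trial is not ordinary care alone. It also contains the part of the iQuit questionnaire completed before allocation, which the report cannot be generated without. A comparison of the two arms removes that part from both sides.

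Any resulting error goes one way: iQuit looks quicker to deliver than it would be in a practice that did not already ask these questions. The account of the pilot, under Text messaging, reports that the program lengthened consultations, so consultation time is a known burden. It is also the only cost measure named, in a trial meant to inform whether a larger effectiveness and cost-effectiveness trial should follow.

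**Working it through.** The article states no consultation time or cost, so there is no figure to reproduce. The check is an accounting of what each consultation contains, followed by item counts.

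**Content of each consultation** (Control; Intervention; Procedure: initial consultation; Randomisation)

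- Intervention = usual care + Part 1 + Part 2 + report handling + research tasks
- Control = usual care + Part 1 + research tasks
- Difference = Part 2 + report handling

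Here usual care + Part 1 means their combined time, with shared content counted once. Consent and case report forms occur in both arms and should largely cancel.

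**Target quantity**

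- Added time over usual care = (1 − v) × Part 1 + Part 2 + report handling, where v is the share of Part 1 already covered in usual care.
- Shortfall = (1 − v) × Part 1.

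The shortfall is zero if v = 1 and positive otherwise.

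**Item counts**

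- Whole questionnaire: 30 items (Advice report section).
- Part 2: 17 items (Procedure: initial consultation).
- Part 1: 30 − 17 = 13 items, taking the 30 to cover both parts. The topic list in the Advice report section includes Part 1 topics, which supports that reading.

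**Shortfall as a share of added questionnaire time** (equal time per item assumed, report handling left out)

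| Overlap v | Items in the difference | Items added over usual care | Shortfall |
|---|---|---|---|
| 0 | 17 | 17 + 13 = 30 | 13/30 = 43% |
| 0.5 | 17 | 17 + 6.5 = 23.5 | 6.5/23.5 = 28% |
| 1 | 17 | 17 | 0% |

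**Sensitivity to report handling.** Report time is in the difference, so including it lowers the percentage. Take an assumed 2 minutes for the report and 20 seconds per item, with v = 0:

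- Difference: 17 × 20/60 + 2 = 7.67 minutes.
- Full added time: 7.67 + 13 × 20/60 = 12.0 minutes.
- Shortfall: 1 − 7.67/12.0 = 36%.

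Over an assumed 10 to 30 seconds per item, the shortfall is 31% to 38% with no overlap and 18% to 24% with half overlap. In minutes, the cancelled Part 1 time with no overlap would be 13 × 10/60 = 2.2 to 13 × 30/60 = 6.5. These times are illustrations; nothing in the article supports one value over another.

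**The case against.** Several points on the other side have force.

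- **No formula is stated.** The cost sentence mentions the two conditions without a subtraction, and an analysis plan is to follow. This stands in part. Speaking of an increase in length does imply a contrast between the arms, and neither the cost nor the feasibility wording says that Part 1 time will be added back.
- **The timing data are already planned.** Correct: Part 1 and Part 2 are logged separately, and audiotapes exist for a sample. Nothing is lost, and only the definition needs repair.
- **Part 1 also serves the trial and resembles usual care.** Its stated purposes include describing the sample and checking baseline balance. Cigarette consumption, longest abstinence, quit date and the CO entry are close to what advisers already cover. This stands, and it is why the range begins at 0%.
- **Costing is deferred.** The Discussion leaves fuller costing to the later trial. A reader might infer that the present plan is wrong to omit the cost of text messaging. The documents do not support that: a staff-time measure is a legitimate limited choice in a proof-of-concept trial, provided it is labelled as such.

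A reader might also infer that the added time is understated by 43%, or that all of Part 1 should count as delivery time. Neither follows, because both assume no overlap with usual care. Nor would this measure alone settle whether a larger trial proceeds: the Sample size section ties that decision to the posterior probability for the six-month relative risk.

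**Conclusion.** The point holds as a bounded one. Compared between arms as described, consultation length gives Part 2 plus report handling, not the full time iQuit adds to usual care. The error is zero or in iQuit's favour. By item count it lies between 0 and 13 of 30 items, that is 0% to 43% of questionnaire time, assuming equal time per item and that the 30 items span both parts. With report handling included, the percentage of total added time is smaller.

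The direction follows from the documents; the size in minutes does not. The Discussion also raises the possibility of compensatory advice to controls, which would shrink the difference further.

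Only a feasibility measure and an additional cost analysis are affected. The primary outcome, the quit-rate analyses and the power are not.

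**What to change.** Make three changes of wording, in the analysis plan or the article:

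1. State that the between-arm difference in consultation length is a lower bound for added delivery time, because controls complete Part 1.
2. Report the difference plus the program-logged Part 1 time as the upper bound, for both the feasibility and the cost measure. Note that this overstates the added time where Part 1 repeats usual care, and that the bounds concern Part 1 only, not compensatory advice to controls.
3. Describe the cost measure as adviser consultation time, not the cost of the whole intervention. No text-messaging cost analysis is needed.

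The cost is a few sentences and one extra row in a table. The Part 1 times are already to be recorded. Report handling needs no separate timing, because it is already inside the difference.

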### Ethical approval

Ethical approval for the trial was granted by Cambridgeshire 2 Research Ethics Committee (REC reference number: 09/H0308/87).

## Discussion

The objectives of this trial are to assess acceptability, feasibility and short-term effectiveness of the iQuit in Practice intervention. The intervention needs to be acceptable to the SCAs who deliver it (the tailored advice report) and to the participants who receive it (the tailored advice report and the tailored text messages). Acceptability to the SCAs will be assessed by both postal questionnaires and semi-structured interviews. These will also address aspects of feasibility, along with measures such as the number of smokers per practice recruited into the study in a six-month period. Acceptability to the participants will be assessed by postal questionnaires and by measures of how they engage with the text messaging programme, for example the proportion who opt to stop receiving text messages.

With regard to effectiveness, we designed the trial to maximise both internal and external validity. The participant will be randomised by computer program during the consultation. The allocation sequence will not be accessible to the SCAs or to the participants. However, as soon as the participant has been randomised, both the SCA and the participant will know which group the participant has been allocated to. If the participant is allocated to the intervention group, the SCA will ask the participant more questions and enter the answers on the online questionnaire. They will then print out the tailored advice report and give it to the participant. The content of the remainder of the consultation should be identical for intervention and control participants. However, given that both SCA and participant will become unblinded during the consultation, it is possible that there will be systematic differences between intervention and control conditions in the usual care component in the later part of the consultation; for example, SCAs may unwittingly or deliberately provide additional advice to control participants to compensate for them having been allocated to this condition, or control participants may ask what advice they would have received had they been allocated to the intervention group. Such effects may dilute differences between groups. A sample of intervention and control consultations will be audiotaped so that the content of the consultations can be compared, which may allow us to detect (though not prevent) this possible source of performance bias.

Outcome assessment will be by postal questionnaire or by telephone interview conducted by a research interviewer. The interviewer will initially be blinded to the participant’s group allocation, and the primary outcome will be assessed at the start of the interview, but the interviewer will become unblinded during the interview when they ask about the intervention. Whether the primary outcome is collected by questionnaire or interview, there is a risk of bias when the outcome is based on self-report and participants know their group allocation. Use of an objective measure would in principle eliminate outcome assessment bias. We carefully considered whether to try to obtain saliva samples by post for cotinine assay, but decided against this because it has several disadvantages; for example, it may yield a low response rate.

In this trial, external validity is increased by using health professionals (practice nurses and health care assistants) rather than research staff to deliver the intervention (tailored advice report) and the control intervention (usual care) in a general practice setting and by employing minimal exclusion criteria for both practices and patients. The tailored advice report component of the intervention was designed to be easily integrated into a usual care consultation and the text messaging component to be delivered independently of the general practice setting.

The findings of the trial will be used to refine the intervention and to inform the decision to proceed to a pragmatic trial of effectiveness and cost-effectiveness. Such a trial would include a more detailed assessment of costs, and the primary outcome for effectiveness would be assessed at 6 or 12 months. We would consider using a cluster randomised design (with practice as the cluster) instead of individual randomisation, and we would attempt to minimise the time that the SCAs spend on research procedures in the consultation and to reduce the measurement burden for participants and SCAs.
